### EQ-5D Health States and Observed EQ VAS Values

In addressing the first research question, the proportion of problems (no problem [level 1], some problems [level 2], and severe problems [level 3]) for each dimension and observed EQ VAS values of patients, at baseline and 1-year follow-up, will be compared across and within the patient groups (as well as subgroups based on diagnosis groups) and with the general population data. These descriptive analyses will also be presented by age groups, sex, BMI, and American Society of Anesthesiologists (ASA) physical status classification system (for patient groups with data on ASA class; Tables 1 and 2). Comparison of EQ VAS values by sex in the different patient groups, controlling for age, will be performed using analysis of covariance. Cluster analysis will be performed to assess the distribution of the EQ VAS value in the different patient groups at both baseline and 1-year follow-up.

Furthermore, pooled data from all NQRs will be used to analyze EQ VAS and to explore the influence of both patient characteristics and the patient group (registers). This will be performed by accounting for the grouping of patients by register. Linear mixed effects models with the patient group, preoperative EQ VAS (for the analysis at 1 year and the change from baseline), intervention type, age, and sex as fixed effects, and the patient group as the random effect will be used. Age and sex have been shown to influence EQ VAS values in previous studies [68,69].

Change over time in terms of the proportions of problems reported in each dimension will be presented using the Paretian Classification of Health Change, introduced to apply the Pareto Principle to EQ-5D health states [70]. This analysis will be performed by calculating the proportions of changes in health states from baseline to 1-year follow-up. The changes will be categorized as “no problem” (health state 11111 at both baseline and 1-year follow-up), “no change” (same health state at both baseline and 1-year follow-up), “improved” (improvement in at least one dimension without worsening in any other), “worsened” (worsening in at least one dimension without improvement in any other), and “mixed” (a mix of improvement and worsening) [70]. These changes will be analyzed descriptively in different patient groups and subgroups. In addition, changes in EQ VAS in the Paretian Classification of Health Change categories will be analyzed.

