### Data Sources

Data from 12 NQRs on about 700,000 patients with PRO records will be included from the over 1.4 million patients in the registers. Clinical data (age, sex, BMI, diagnosis/es, and interventions) and PROs data (EQ-5D-3L, and EQ-5D-5L) will be retrieved from the registers. Data from cross-sectional population surveys in Sweden will be included for comparison; about 45,000 records were used in developing the Swedish experience-based VAS and TTO value sets [26]. The registers included in the project are described in Tables 1 and 2.

**Table 1 table1:** General information on the 12 National Quality Registers [57,67].

Register	Diagnosis/condition	Intervention^a^	Start year	Unique patients^b^	New entries per year^b^
Better management of patients with Osteoarthritis (BOA)	Hip, knee, hand osteoarthritis	Supported Osteoarthritis Self-Management Programme (SOASP)	2008	110,000	18,000
Swedish Ankle Registry (Swedankle)	Osteoarthritis and inflammatory conditions in the ankle	Total ankle arthroplasty, ankle arthrodesis procedures	1997	4000	400
Swedish National Anterior Cruciate Ligament Register (xBase)	Cruciate ligament injuries	Cruciate ligament surgery	2005	46,000	4000
Swedish Fracture Register (SFR)	All types of fractures including vertebral/spinal fractures	Surgical and nonsurgical treatments	2011	430,000	82,000
Swedish Heart Failure Registry (SwedeHF)	Chronic heart failure	Pharmacological treatment, physical activity	2003	92,000	9500
Swedish Hip Arthroplasty Register (SHAR)	Hip osteoarthritis and other hip joint diagnoses	Hip replacement	1979	370,000	25,000
Swedish Knee Arthroplasty Register (SKAR)	Knee osteoarthritis and other knee joint diagnoses	Knee replacement	1975	220,000	16,000
Swedish National Quality Register for Bipolar Disorder (BipoläR)	Bipolar affective disorder	Pharmacological treatment, patient education	2004	21,000	1500
Swedish National Registry for Respiratory Failure (Swedevox)	Respiratory failure	Long-term oxygen therapy	1987	20,000	1200
Swedish Rheumatology Quality Register (SRQ)	Rheumatic diseases	Medical treatment, rehabilitation	1995	80,000	7000
Swedish Spine Register (Swespine)	Spinal stenosis, disk hernia, and other spinal diagnoses	Spine surgery	1993	130,000	10,000
Swedish Registry for Systematic Psoriasis Treatment (PsoReg)	Psoriasis	Systemic treatment for psoriasis	2007	6500	500

^a^An intervention refers to surgeries or other forms of treatments provided to patients in the registers.

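### The pooled mixed model for EQ VAS enters register as both a fixed and a random effect, so the register variance is not identifiable and the standard errors of register contrasts are not set by the data

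*Protocol article*

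**What the plan says.** The specification is in the protocol article, Methods, EQ-5D Health States and Observed EQ VAS Values. Data from all registers are pooled to "explore the influence of both patient characteristics and the patient group (registers"). The text then says "This will be performed by accounting for the grouping of patients by register".

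The model sentence opens "Linear mixed effects models with the patient group, preoperative EQ VAS" and ends "intervention type, age, and sex as fixed effects, and the patient group as the random effect will be used". Patient group is therefore the first fixed effect and also the only random effect. No random slope, and no unit other than register (hospital, diagnosis subgroup), is named that would give the random term another meaning.

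The number of levels comes from Data Sources: "Data from 12 NQRs on about 700,000 patients with PRO records will be included". Table 1 in that section gives each register's interventions. Seven registers (BOA, xBase, SHAR, SKAR, Swedevox, Swespine, PsoReg) list a single one found in no other register. The fracture register's entry is "Surgical and nonsurgical treatments".

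**The concern.** A factor can be fixed, so that its levels are compared with each other, or random, so that its levels are summarised by a variance. Giving one factor both roles as an intercept leaves the variance with nothing to explain, because the fixed indicators already absorb every difference between registers. That variance nevertheless enters the standard error of each register contrast.

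This is the only adjusted model planned for the effect of patient group on EQ VAS, which is part of the first research question. If it is fitted as written, two analysts with the same data could report the same register difference with very different confidence intervals.

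Intervention type raises a second, conditional problem. If its levels follow Table 1, most of them coincide with a register.

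**Working it through.** The plan gives no variance, sample size or expected result for this model, so there is no figure to reproduce. The check is algebra, then a numerical confirmation.

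**Algebra.** Write y = Xb + Zu + e, with register variance s_u² and residual variance s_e². Z holds the 12 register indicators, and X contains the same columns.

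- REML uses only contrasts K'y with K'X = 0. Z lies inside the column space of X, so K'Z = 0 as well, and the REML likelihood does not contain s_u².
- Under ML the residual quadratic form does not change with s_u², but the term -½ Σ log(s_e² + n_k s_u²) falls as s_u² grows. The maximum is at s_u² = 0.
- The variance of a contrast between registers 1 and 2 is, apart from covariate adjustment, 2s_u² + s_e²(1/n_1 + 1/n_2). The first part is the one the data cannot inform.

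None of this depends on an assumed SD or sample size.

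**Numerical confirmation.** Assumed: 12 registers of 200 patients, residual SD 18 (estimated in the sample as 17.58, so s_e² = 309.15), true register SD 6 (variance 36), with age, sex and baseline EQ VAS as covariates.

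| s_u² | REML, fixed + random | ML, fixed + random | REML, random only | SE of one contrast, fixed + random |
|---|---|---|---|---|
| 0 | -8078.3510 | -8073.110 | -8194.604 | 1.76 |
| 1 | -8078.3510 | -8076.104 | -8153.139 | 2.26 |
| 9 | -8078.3510 | -8084.631 | -8109.071 | 4.59 |
| 36 | -8078.3510 | -8092.250 | -8104.175 | 8.67 |
| 100 | -8078.3510 | -8098.220 | -8106.722 | 14.25 |
| 400 | -8078.3510 | -8106.469 | -8113.002 | 28.34 |

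- Contrast SE at s_u² = 36: sqrt(2 × (36 + 309.15/200)) = 8.67.
- ML drop from 0 to 36: ½ × 12 × ln((309.15 + 200 × 36)/309.15) = 6 × 3.19 = 19.14, which matches 8092.250 - 8073.110.
- The contrast estimate stayed at -2.621 throughout. The SEs for age, sex and baseline EQ VAS stayed at 0.0299, 0.720 and 0.0181.
- With register random only, the likelihood is informative and, on this grid, highest at the true value of 36.

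A Python mixed-model routine was also fitted to three further simulated data sets (true variance 36, age as the only covariate). With register in both roles, REML returned 319 to 324 with a contrast SE of 25.3 to 25.5 and no warning. ML returned 0 with an undefined SE and convergence warnings.

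**Illustration with Table 1 totals.** Take 4,000 (Swedankle) and 20,000 (Swedevox) patients and an assumed residual SD of 20. With fixed effects only, SE = sqrt(400 × (1/4000 + 1/20000)) = 0.35. Adding 2s_u² for assumed register SDs of 2, 5 and 10 gives 2.8, 7.1 and 14.1.

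**Intervention type.** Taking each Table 1 label as a level gives 12 registers, 16 labels and 17 register-label combinations: seven registers with one label and five with two. Estimating both factors needs rank 12 + 16 - 1 = 27; the design has rank 17. Register uses 12, so 5 intervention contrasts remain instead of 15, all of them within a register. With an assumed surgical/nonsurgical coding the rank is 13 of 13, but on Table 1 only SFR contains both levels.

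**The case against.** The best defence is that the damage is narrow, and much of it stands.

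- **Estimates.** A reader might infer that the whole model is uninterpretable. It is not: contrast point estimates and patient-level coefficients do not move with the register variance, so the patient-characteristics half of the aim is intact.
- **Estimator.** Under ML the variance goes to zero and the model is in effect the fixed-effects model. The article names no estimator, which an article may leave to a fuller plan. But a specification that is sound only if one of its terms vanishes is still mis-stated, and the ML fits above gave no usable standard error.
- **Software.** The article plans SAS and R. The fits above used Python, so the particular values returned say nothing about those programs. The flat likelihood holds in any software.
- **Scope.** A reader might take this as the only adjusted analysis for the first research question. The same section also plans an age-adjusted analysis of covariance by sex, which is unaffected. The value-set analyses for the other research questions do not use this model.
- **Intervention type.** A reader might conclude that it is nested in register and cannot be estimated. The documents do not support that: pharmacological treatment appears under both SwedeHF and BipoläR, Table 1 is a summary, interventions are retrieved as clinical data, and the coded levels are not given.
- **Size.** A reader might quote an 8- to 41-fold inflation from the Table 1 illustration (2.8/0.35 to 14.1/0.35, before rounding). That is not an expected effect. The SDs are chosen, and the sizes are register totals rather than patients with complete baseline and 1-year data.

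The double role of register itself has no answer in the document.

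**Conclusion.** The model is wrong as written on one point: register is both a fixed effect and the random effect, so its variance is not identifiable under REML and is zero under ML. What is affected is the standard errors and confidence intervals of register contrasts and any reported between-register variance. The conclusion rests only on patient group meaning register, as the section itself says, and on the random effect being an intercept, since no slope is named. The numerical sizes rest on assumed SDs and register sizes and show direction only.

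The intervention-type point is conditional. It holds largely if the levels follow Table 1. If they are surgical versus nonsurgical, the effect is estimable but, on Table 1, informed by SFR alone.

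This should be corrected before results from this model are reported. It does not undermine the study as a whole.

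**What to change.** Use register once in each model.

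1. For register contrasts, enter register as a fixed effect and delete the register random intercept.
2. If the between-register share of variance is wanted, fit a separate model with register random only and report the intraclass correlation.
3. State the levels of intervention type. If they largely coincide with register, estimate its effect within those registers that have more than one coded type in the data, rather than as a main effect across registers.

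Moving the random intercept to the patient is not a substitute. The 1-year and change models have one outcome per patient, so a patient intercept is confounded with the residual unless people recur across registers, which the article does not address.

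The cost is analysis wording and a refit of any pooled model already run in both roles, since the article reports that analysis is under way. No new data are needed.

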^b^Information on the number of patients and new entries per year was received from registers.

**Table 2 table2:** EQ-5D data collected at the 12 National Quality Registers [57,67].

Register	Follow-up times
Better management of patients with Osteoarthritis (BOA)	First visit, 3 and 12 months; 1, 2, 3, 4, 5, 6, and 7 years after (100 patients per year are randomized to continued follow-ups)
Swedish Ankle Registry (Swedankle)	Before surgery, 6 months, 1 and 2 years after
Swedish National Anterior Cruciate Ligament Register (xBase)	Before surgery, 1, 2, 5, and 10 years after
Swedish Fracture Register (SFR)^a^	A week before injury (recall) and 1 year after
Swedish Heart Failure Registry (SwedeHF)	At new visit, within 6 months and 1 year, once every year
Swedish Hip Arthroplasty Register (SHAR)	Before surgery, 1, 6, and 10 years after
Swedish Knee Arthroplasty Register (SKAR)	Before surgery, 1 year after
Swedish National Quality Register for Bipolar Disorder (BipoläR)	At visit
Swedish National Registry for Respiratory Failure (Swedevox)	At treatment start, 1 year after
Swedish Rheumatology Quality Register (SRQ)	At visit
Swedish Spine Register (Swespine)	Before surgery, 1, 2, 5, and 10 years after
Swedish Registry for Systematic Psoriasis Treatment (PsoReg)	At each revisit due to psoriasis/visit to the skin clinic/telephone conversation with a dermatologist

^a^Baseline data in SFR are collected by a recall of a few weeks after the occurrence of fracture.

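### The pooled mixed model gives 12 unlike registers one baseline EQ VAS slope, one age slope and one sex effect, and enters patient group as both fixed and random

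*Protocol article*

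**What the plan says.** Under EQ-5D Health States and Observed EQ VAS Values, the pooled analysis is meant "to explore the influence of both patient characteristics and the patient group (registers"), and "This will be performed by accounting for the grouping of patients by register". The model is a linear mixed model. Its list of fixed effects opens with patient group and, when the outcome is 1-year EQ VAS or its change, the baseline value. The list closes with "intervention type, age, and sex as fixed effects, and the patient group as the random effect will be used". Patient group therefore appears among the fixed effects and again as the random effect. Nothing is said of interactions or random slopes.

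Two other places bear on this. The same section plans a sex analysis that is not pooled: "Comparison of EQ VAS values by sex in the different patient groups, controlling for age, will be performed using analysis of covariance". In Data Sources, the Table 2 footnote on the Swedish Fracture Register (SFR) says "Baseline data in SFR are collected by a recall of a few weeks after the occurrence of fracture", and the table gives the time point as a week before injury. Other registers record baseline before surgery, at treatment start or at a visit.

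**The concern.** Table 1 puts joint replacement, ligament and spine surgery beside heart failure, bipolar disorder, rheumatic disease, psoriasis, long-term oxygen therapy and fractures. Baseline EQ VAS does not mean the same thing throughout: it is health before an operation in some registers, health during chronic disease in others, and recalled pre-injury health in SFR. The article calls it preoperative although several registers involve no operation. There is little reason to expect 1-year EQ VAS to follow it with the same slope everywhere.

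Two outputs are at stake. The first is the set of register contrasts at 1 year and for change, which would mix real differences in level with differences in slope. The second is the pooled effects of patient characteristics, reported as single numbers with very small standard errors. Nothing else in the article fits the baseline EQ VAS slope by register.

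**Working it through.** The article states no standard error, effect size or slope for this model, so there is no figure to reproduce. The checks ask how much a common slope could matter.

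**Inputs from the article.** There are 12 registers and about 700,000 patients with patient-reported outcome records. The Table 1 counts sum to 1,529,500, of which SFR is 430,000 (28%). SFR, hip and knee arthroplasty together are 1,020,000 (67%).

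**Assumptions.** Records with patient-reported outcomes are proportional to Table 1 counts. Residual SD is 20, baseline EQ VAS SD 20, age SD 12, and half are women. The common baseline slope is 0.4, and register baseline means vary with SD 8. Tau is the SD of the true effect between registers.

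**1. Register contrasts.** Write b_g for a register's own slope, b for the common slope, m_g for its mean baseline and x0 for the reference baseline. The common-slope adjusted mean differs from the own-slope one by

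(b_g − b) × (m_g − x0).

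For example, a slope gap of 0.10 and a mean 8 points from the reference give 0.10 × 8 = 0.8 points. Both factors must be non-zero.

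The simulation set no true register difference at x0 and used 700,000 records and 60 runs per setting:

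| tau | pairs significant at 5% | median absolute difference | 90th percentile |
|---|---|---|---|
| 0 | 5% | 0.14 | 0.48 |
| 0.05 | 39% | 0.33 | 1.05 |
| 0.10 | 59% | 0.57 | 1.87 |

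With equal baseline means, the rate stayed at 5% even at tau 0.10 (run at one-tenth of the records).

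**2. Standard errors of the pooled effects.**

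- Model SE = residual SD / (covariate SD × √N). For baseline EQ VAS this is 20/(20 × √700,000) = 0.0012; for age, 20/(12 × √700,000) = 0.0020; for sex, 20/(0.5 × √700,000) = 0.048.
- SE for the mean effect over a population of registers = √(SE² + tau² × Σw²), with w the register shares. Here Σw² = 0.178, equivalent to about 5.6 equal registers.
- Example, baseline slope at tau 0.05: √(0.0012² + 0.05² × 0.178) = 0.0211, about 18 times the model SE.

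| effect | tau | SE ratio |
|---|---|---|
| baseline EQ VAS | 0.02 / 0.05 / 0.10 | 7 / 18 / 35 |
| age, per year | 0.02 / 0.05 / 0.10 | 4 / 11 / 21 |
| sex, points | 0.5 / 1 / 2 | 4.5 / 9 / 18 |

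For the baseline slope, nominal 95% intervals would cover the typical-register value 22%, 9% and 4% of the time. For the size-weighted average of these 12 registers, simulated coverage was 93% to 97% at every tau tried.

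**3. Patient group fixed and random.** In a small illustrative data set with 12 groups, the REML log-likelihood was −2019.1077 whether the register variance was set to 0, 1, 9, 100 or 1000. The data therefore carry no information on that variance. The SE of a register contrast rose from 4.1 to 44.9 over the same values, while the slope SE stayed at 0.0424.

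**4. Precision cost of own slopes.** The smallest register, the ankle register, scales to 1,831 records. Its own-slope SE is 20/(20 × √1,831) = 0.023. Read 8 points from its own mean, the SE of its adjusted mean goes from 20/√1,831 = 0.47 to √(0.47² + (8 × 0.023)²) = 0.50. Its own sex effect has an SE of 20/(0.5 × √1,831) = 0.93 points. Large registers lose almost nothing.

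**The case against.** The article is condensed. It does not say that the random part is an intercept only or that interactions are excluded, and such detail can sit in an analysis plan. That tempers the point, but the model is spelled out term by term, and main effects with a register intercept are its natural reading.

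A reader might infer that the model will produce spurious register differences and far too narrow intervals. The article does not support this, for four reasons:

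- It gives no slopes, baseline means or heterogeneity. Unlike conditions and a recalled baseline make unequal slopes plausible, not established.
- A harsher assumed scenario (slopes of 0.3 in surgical and 0.5 in other registers, or 0.2 and 0.6; baseline means 47 to 80) gives spreads of 3.6 and 6.7 points. These are highest minus lowest over 12 registers, not a typical pair. Once slopes differ, registers truly differ at every baseline except the chosen reference, so false means false at that reference only.
- The narrow standard errors are wrong only for a typical-register effect. For the size-weighted average of these 12 they are about right.
- The register shares rest on all-time Table 1 counts. The shares with complete baseline and 1-year data are not given.

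A reader might also infer that the plan contradicts itself on sex. It does not: the analysis of covariance in the different patient groups complements the pooled model and already shows sex effects by group. The pooled model is moreover an exploratory addition to the descriptive comparisons. What stands is that register-specific baseline slopes are examined nowhere, and that patient group is entered twice.

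**Conclusion.** The point holds in a limited form. As written, the pooled model allows no difference between registers in the effects of baseline EQ VAS, age or sex. If these effects and the baseline means do differ, register contrasts at 1 year and for change will carry slope differences and depend on where they are read. The pooled effects will then describe a size-weighted average of these registers, not a typical one. The article cannot settle the size: there is no harm with equal slopes, and in the scenarios with slope SDs of 0.05 and 0.10 the register differences were mostly under 2 points on the 0-100 scale, though often statistically significant at this sample size. The several-fold understatement of standard errors applies only to generalising across registers and rests on the assumed values of tau.

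The double entry of patient group needs no such assumption: it leaves the register variance unidentified and makes the standard errors of register contrasts arbitrary. The change is worth making, since it alters little if slopes are equal.

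**What to change.** - Enter patient group once, as a fixed effect.
- Add patient-group interactions with baseline EQ VAS (in the 1-year and change analyses), age and sex.
- Report register contrasts at stated baseline EQ VAS and age values, limited to ranges where the compared registers overlap.
- Tabulate register-specific slopes and sex effects. If a pooled effect is also given, say that it is a size-weighted average over these 12 registers.

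Splines for age and random slopes are optional.

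The cost is 3 × 11 = 33 extra coefficients in the follow-up models and 2 × 11 = 22 at baseline, plus fuller tables. The loss of precision is negligible except in the smallest registers, where register-specific effects will be visibly less certain. No new data are needed.
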